### Outcome measures

#### Primary outcomes

The primary outcomes relate to the assessment of skin function and structure:
1.*Cutaneous microvascular function.* This will be assessed using the combination of cutaneous microdialysis and laser Doppler flowmetry.2.*Cutaneous sudomotor function.* This will be examined using cutaneous microdialysis combined with capacitance hygrometry.3.*Cutaneous blood vessel and sweat gland size.* This will be assessed using the skin punch biopsy technique and confocal microscopic imaging.

#### Secondary outcomes

Anthropometric data (e.g., height and weight), age and ethnicity will be collected. Resting blood pressure will be recorded at baseline and at intervals throughout the first visit. A single venous blood sample will be collected at the first visit to measure oestradiol and circulating pro-inflammatory markers.

### Experimental design

This is a parallel group design where participants will attend the laboratory on two separate occasions. The first visit will consist of anthropometric measurements and a blood sample, followed by assessment of post-ganglionic skin blood vessel and sweat gland responsiveness (cutaneous microdialysis). At the second visit (∼7 days later), participants will undergo a skin punch biopsy.

#### Visit 1: skin and sweat gland function

To minimise acute hormonal fluctuations, participants in the premenopausal group will attend for their first visit during the early follicular phase (days 1–5) of their menstrual cycle. To control for diurnal variation, testing will commence at 8.30am, lasting approximately 3–4 h. Participants will fast overnight and will be instructed to abstain from caffeine, alcohol, carbonated drinks for 12 h prior to testing, only drinking water. Participants will also be asked to avoid moderate/vigorous exercise for 24 h before testing. Ambient temperature in the laboratory will be controlled at 22°C–24°C (26).

##### Anthropometrics

Upon arrival, height and weight (Seca, Birmingham, U.K.) will be measured.

##### Blood pressure (BP)

Participants will rest in a seated position for ∼10 min prior to measuring their resting BP using an autosphygmomanometer (Dinamap V100, GE Healthcare, Chalfont St. Giles), with the BP cuff wrapped around the contralateral (dominant) arm to where skin function will be assessed. BP will then be measured in triplicate, leaving 1 min between successive measurements. BP will subsequently be recorded at 10 min intervals during the experimental protocol.

##### Blood sample

A single 8 ml blood draw will be taken from the antecubital fossa on the contralateral (dominant) arm to where skin function will be assessed. Blood samples will be centrifuged (2,500 RCF for 15 min at 5°C) and will be subsequently stored in aliquots at −80°C until analysis. Samples will be analysed using commercial enzyme-linked immunosorbent assays (ELISAs) for oestradiol (Merck, Dorset, U.K.), calcitonin gene-related peptide (CGRP; Bertin Bioreagent, Montigny le Bretonneux, France), prostaglandin 2E (Invitrogen) and a multiplex assay will be used to analyse circulating levels of inflammatory markers (MILLIPLEX, Merck, Dorset, U.K.).

##### Cutaneous microdialysis

Participants will rest in a supine position with ice applied topically to the non-dominant forearm for ∼10 min to acutely numb the non-dominant forearm, prior to insertion of a 25-gauge needle in the dermal space at a depth of 0.3–1.0 mm (27) (exiting 20 mm from the entry point) at three sites on the forearm, separated by >3 cm. An intradermal microdialysis membrane (Linear 30; CMA Microdialysis Ltd., Stockholm, Sweden) with 10 mm window, will then be threaded through the lumen of each needle, with each needle subsequently removed to leave the membrane *in situ* (Figure 1). Following successful placement of the membranes, lactated Ringer's solution will be perfused at 2 µl/min via a syringe infusion pump (Model 11 Plus, Harvard Apparatus, Natick, Massachusetts, USA). Following this, custom-made sweat capsules (3.0 × 2.0 × 1.2 cm) with integrated laser Doppler flowmetry probes (Perimed 413, Periflux 5001 System, Stockholm, Sweden) will be placed above each of the three embedded microdialysis membranes for the simultaneous quantification of skin blood flow (28) and sweat rate (SR) via capacitance hygrometry (HMT330, Vaisala, Vantaa, Finland) using compressed nitrogen gas at a flow of 300 ml/min (29). Absolute humidity of each capsule will be converted to SR from gas flow and the capsule surface area. Cutaneous vascular conductance (CVC) will be calculated [flux/mean arterial BP].

**Figure 1 F1:**
[figure not shown]
Illustration of the microdialysis technique and apparatus. Created in BioRender. [name] (2025). https://BioRender.com/ouwrev6.

Following microdialysis membrane placement and allowing for its associated hyperaemic response to subside (≥90 min), baseline CVC and SR will be collected for 5 min. Each membrane will subsequently be randomly assigned and perfused with one of the following: increasing doses of CGRP (1 × 10^−11^–10^−4^; 8 doses at 10-fold increments) dissolved in Ringer's solution, acetylcholine (Ach; 1 × 10^−7^-1M; 8 doses at 10-fold increments) dissolved in Ringer's solution, or sodium nitroprusside (SNP; 1 × 10^−7^-50 mM; 8 doses at 10-fold increments) dissolved in Ringer's solution. Each dose will be administered for 7 min (1 min at a perfusion rate of 5 µl/min and 6 min at 2 µl/min). Following the last dose, 50 mM SNP will be perfused through each membrane for 10 min to initiate peak vasodilation at each of the assessed sites (29).

Data will be continuously sampled at 50 Hz (PowerLab, ADInstruments, Oxford, UK) and recorded online (LabChart, ADInstruments, Colorado Springs, Colorado, USA). For each dose, CVC and SR will be averaged at 10 s intervals, and the 60 s average around the maximum 10 s value from each stage will be selected for analysis (29).

A between groups statistical analysis of the pre- and postmenopausal cohorts will be conducted in a blind manner. Exploratory analyses using a linear mixed model with fixed effects of drug dose (cutaneous microdialysis) and/or group will be conducted. Dose-response curves for CVC and SR at each of the three microdialysis sites will be constructed using a nonlinear fitting technique, from which the effective concentration causing 50% of the maximal response (EC_50_) will be identified (Prism, GraphPad Software). *Post hoc* comparisons across drug doses or between groups will be completed using Bonferroni adjusted LSD. Effect estimates with a 95% confidence interval for differences between groups, as well as changes within groups over drug doses, will be reported.

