### Eligibility criteria

Potential participants will exclude themselves based upon the detailed inclusion/exclusion criteria (Table 1) provided on recruitment material and the PIS. These criteria reflect the practical requirements of the study, to ensure that research findings are valid and to ensure the safety of participants. Participants will be consented and screened, consisting of medical history and details of current medications. Postmenopausal participants will complete a 7-day hot flush diary (25). Members of the research team will review completed screening information to confirm eligibility to participate.

**Table 1 T1:** Detailed inclusion and exclusion criteria.

Detailed inclusion criteria		
Postmenopausal + Hot Flush	Postmenopausal	Premenopausal
• Female • Aged 45–65 years • Amenorrhoeic for >6 months • >4 Hot flushes per day • Not on medication or treatments to alleviate hot flushes e.g., HRT	• Female • Aged 45–65 years • Amenorrhoeic for >6 months	• Female • Aged 18–40 years • Eumenorrheic
AND		
• Healthy • Non-smoker/non-vaper • BMI 18–30 kg/m^2^ • No history of cardiovascular or respiratory disease • No history of metabolic diseases e.g., type II diabetes • Drink <14 units of alcohol per week • Participant is willing and able to give informed consent for participation in the study.		
Detailed exclusion criteria		
• Cannot readily read and understand English • Aged <18 years, 41–44 years or >65 years • Male • Current smoker/vaper • BMI <18 or >30 kg/m^2^ • Medical history of cardiovascular/respiratory disease • Medical history of metabolic disease e.g., type II diabetes • Drink >15 units of alcohol per week • Vaccination (<1 week) due to induced systemic inflammatory reaction • Local forearm infection • Allergy to local anaesthetic/Marcaine/amide-group anaesthetics • Currently pregnant, or planning on becoming pregnant • <6 Months postpartum or stopped breast feeding <1 month before recruitment • On medication or treatments to alleviate hot flushes or have taken such medication/treatments within the previous 6 months e.g., HRT		

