## Discussion

The aim of this novel study is to examine both function and structure of skin blood vessels and sweat glands in pre- and postmenopausal women, who do and do not experience hot flushes. Findings from this work will reveal whether menopause is associated with altered function of skin blood vessels and sweat glands, such as an overt sensitivity to vasoactive substances that contributes to hot flushes. Furthermore, the study will examine whether menopause affects the structure of skin blood vessels and/or sweat glands, and whether a relationship exists between the function and/or structure of skin blood vessels and/or sweat glands, and the occurrence of hot flushes. Observation of any such changes in function and/or structure would increase our understanding of the causes and side effects of hot flushes, which would have important implications for patients and clinicians by helping in the design of effective treatments. Such therapies may include interventions that can manipulate the activity of the skin blood vessels and/or sweat glands via pharmacological and non-pharmacological methods.

Hot flushes, experienced by ∼80% of postmenopausal women, have a profoundly debilitating effect on daily activities and quality of life (1). Whilst menopausal hot flushes are widely recognised as being extreme thermoregulatory events with episodes typically lasting for several minutes and ranging from a few times per week up to several episodes per hour, their underpinning mechanisms are not well understood which has consequently limited scientific advances in hot flush therapies. Previous work has suggested mechanisms related to a narrowed null zone in the core temperature range of menopausal women reducing the temperature threshold for the onset of sweating, such that sweating will be activated and a hot flush triggered when an increase in core temperature surpasses the lowered threshold (34). However, this hypothesis is disputed as a further study observed that 49% of women did not experience a subtle increase in core temperature prior to a hot flush (35).

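### The stage-maximum rule would count a spontaneous hot flush as drug response, a modest bias mainly in the hot-flush group; separately, 10-min blood pressure readings miss 2 or 3 of the 8 dose stages

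*Protocol article*

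**What the plan says.** All places are in the protocol article.

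- **Stage value.** Under Visit 1, Cutaneous microdialysis, CVC and sweat rate are averaged in 10 s steps, and "the 60 s average around the maximum 10 s value from each stage will be selected for analysis". The rule serves the first two primary outcomes, microvascular and sudomotor function.
- **Timing.** "baseline CVC and SR will be collected for 5 min", then "8 doses at 10-fold increments" at each site. "Each dose will be administered for 7 min". Afterwards "50 mM SNP will be perfused through each membrane for 10 min".
- **Population.** Table 1 requires ">4 Hot flushes per day" for the postmenopausal hot-flush group. The other postmenopausal column gives sex, age and amenorrhoea, with no upper limit on flushes.
- **Flushes.** The Introduction says that they are often spontaneous and that their key events are reddening and sweating at the skin. The Discussion describes them "with episodes typically lasting for several minutes and ranging from a few times per week up to several episodes per hour".
- **Blood pressure.** CVC is flux divided by mean arterial pressure. Under Blood pressure (BP), "BP will subsequently be recorded at 10 min intervals during the experimental protocol".

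The article does not say what happens to a stage during which a flush occurs, or which pressure reading is used for a stage that contains none.

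**The concern.** A rule that looks for the highest 10 s of a stage will favour a transient rise over the drug plateau. A flush is such a rise, appears in both recorded signals, and lasts a large part of a 7-min stage. Because one group is recruited for frequent flushes, the error differs between groups. At sub-maximal doses it points towards the result that the Discussion anticipates, greater responsiveness in women with hot flushes.

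The article's other safeguards do not remove this. Abstaining from caffeine and alcohol does not prevent spontaneous flushes. A blinded analyst with no flush marks cannot tell a flush from a drug response. A flush would probably lift all three sites in the same stage, so no site serves as a control for another.

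The pressure schedule is a separate and smaller matter. A 10-min cycle cannot supply a reading for every 7-min stage, so some CVC values must borrow a pressure from a neighbouring stage.

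**Working it through.** The plan gives no figure for flush contamination, so there is none to reproduce.

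**Inputs from the article:** eight stages of 7 min, so 8 × 7 = 56 min of dosing; 12 hot-flush women; more than 4 flushes per day at entry; pressure every 10 min.

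**Assumptions:** flushes follow a Poisson process at 4 to 8 per day, spread over 24 h or 16 waking hours; each lasts 3 to 5 min; each adds 30 percentage points of the site maximum to the stage it touches; between-woman SD 15 to 20 points. The article gives none of these except the floor of 4 per day.

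**1. Flush onset during dosing.** P = 1 − exp(−rate × 56 min).

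| Flushes/day | Spread over | Rate per min | P | Women of 12 | P(at least one of 12) |
|---|---|---|---|---|---|
| 4 | 24 h | 0.00278 | 14.4% | 1.7 | 85% |
| 4 | 16 h | 0.00417 | 20.8% | 2.5 | 94% |
| 8 | 24 h | 0.00556 | 26.7% | 3.2 | 98% |
| 8 | 16 h | 0.00833 | 37.3% | 4.5 | over 99% |

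Only the dosing period counts here. Adding the 5 min of baseline and the final 10 min gives 71 min and larger percentages, but those periods are not dose stages.

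**2. A given dose stage touched by a flush.** A flush of length d overlaps a 7-min stage if it starts within a span of 7 + d min, so P = 1 − exp(−rate × (7 + d)).

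- Low end (4/day over 24 h, d = 3): 1 − exp(−0.0278) = 2.7%, or 12 × 0.027 = 0.3 women.
- High end (8/day over 16 h, d = 5): 1 − exp(−0.100) = 9.5%, or 12 × 0.095 = 1.1 women.

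**3. Shift in the group mean at one dose.** P × 30:

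- Low end: 0.027 × 30 = 0.8 points.
- High end: 0.095 × 30 = 2.9 points.

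In SD units this runs from 0.8/20 = 0.04 to 2.9/15 = 0.19, against the effect size of 1 in the sample size section. Simulating a two-sided 5% t-test, 12 against 12, with no true difference and this contamination gives a false-positive rate of about 5.1% to 6.6%.

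**4. EC50.** A simulation added 30 points to one random stage in 25% to 50% of hot-flush women. Mean log EC50 moved by −0.006 to −0.015.

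**5. Pressure coverage.** Readings are 10 min apart and stages 7 min long, so no stage holds two readings. Stages without one = 8 − readings in 56 min.

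- First reading at minute 0 to 5 of dosing: 6 readings, 8 − 6 = 2 stages empty.
- First reading at minute 6 to 9: 5 readings, 8 − 5 = 3 stages empty.

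No moment is more than 5 min from a reading. The article gives no pressure variability from which to size the resulting CVC error.

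**The case against.** The strongest reply is that this is a condensed article. Artefact handling and event marks often sit in a full protocol or operating procedure, and the stage-value rule is referenced to published work. That stands in part: a flush rule may exist elsewhere. But the article fixes the extraction rule in detail, and followed as printed that rule selects the flush.

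The second reply is that the effect is small. This largely stands. High-dose dilation may mask a flush, so adding the full 30 points at every overlap is generous. The mixed model is labelled exploratory, post hoc tests are Bonferroni-adjusted, and EC50 hardly moves.

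Stronger readings are tempting and not supported:

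- A reader might infer that the error occurs only in the hot-flush group. Table 1 sets no flush ceiling for the other postmenopausal group, so it is mainly there.
- A reader might infer that flushes could by themselves create the key group difference. A shift of 0.04 to 0.19 SD does not support that at the rates assumed.
- A reader might infer that the 60 s window certainly runs into the next dose. The wording can also mean a window within the stage. Any spill is at most about half the window and affects all groups alike.
- A reader might infer that the pressure gap biases the comparison. Nothing makes it differ by group, and it does not touch sweat rate.

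**Conclusion.** The point holds as a cheap improvement, not as a threat to the study. As written, a flush during dosing enters the analysis as drug response, mainly in the hot-flush group and, at sub-maximal doses, in the hypothesised direction. Under the stated assumptions this concerns 14% to 37% of that group over the dosing period, but only about 3% to 10% at any one dose, for a shift of roughly 1 to 3 points in a dose-level mean. Flush rates well above 8 per day would enlarge this.

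The absence of a pressure reading in 2 or 3 of 8 stages follows directly from the two schedules if the 10-min cycle runs freely. Its consequence for CVC is minor, non-differential and cannot be sized from the article.

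**What to change.** 1. Mark flush onset and end on the existing LabChart recording, in all three groups. Reliable marks need to be made during the session.
2. Extract stage values with flush-marked segments set aside. Report results with and without them, and the number set aside by group.
3. State that the 60 s window stays within its own stage.
4. Time one pressure reading within each 7-min stage, so that every CVC value has its own mean arterial pressure.

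The cost is a few missing stage values, which the mixed model and curve fit can tolerate, and 8 readings during dosing in place of 5 or 6, so 2 or 3 more per session. If some sessions are already complete, simultaneous rises at all three sites in the stored recordings would allow a flagged sensitivity analysis, and step 3 can still be applied.

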### Sample size calculation

Based on previously reported differences in post-ganglionic skin blood flow responses between postmenopausal women with and without hot flushes (17–19), a power (1-β) of 0.9 and an effect size of 1, 24 postmenopausal women (12 who experience hot flushes and 12 who do not) and 12 premenopausal women will be recruited for this study.

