**Figure 2 F2:**
[figure not shown]
Skin punch biopsy methodology.

Frozen samples will be cut (∼50 microns) and stained with fluorescein-labelled Ulex europaeus agglutinin I, an endothelium-specific antibody (33), and with anti-protein gene product 9.5 (1:1000, anti-PGP 9.5, Chemicon International Inc.), an antibody used to visualise nerve fibres around sweat glands and blood vessels in human skin.

Confocal microscopic imaging of samples (optical sections will be acquired at 2–4 μm intervals throughout the 50 μm section as a z-stack and will be projected in 3D images, Zeiss Axioplan 2, Germany) will subsequently be analysed using ImageJ software (32) to quantify the number and size of the stained blood vessels and the size of the secretory coils of the sweat glands, as well as the number of nerve fibres around the sweat gland within the samples (Figure 2). For between groups analyses (e.g., pre- vs. postmenopausal cohorts), data will be analysed using a one-way ANOVA.

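### The contrast that sized the study, postmenopausal women with versus without hot flushes, is never named in the analysis text, which names only pre- versus postmenopausal cohorts

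*Protocol article*

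**What the plan says.** **Sizing.** The Sample size calculation section starts from "Based on previously reported differences in post-ganglionic skin blood flow responses between postmenopausal women with and without hot flushes", takes "a power (1-β) of 0.9 and an effect size of 1", and concludes that "24 postmenopausal women (12 who experience hot flushes and 12 who do not) and 12 premenopausal women will be recruited". The contrast behind the numbers is therefore hot flushes versus no hot flushes, on skin blood flow.

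**Objectives.** Both objectives under Study aims list premenopausal women and postmenopausal women with and without hot flushes, that is, three groups.

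**Analysis of function (end of the Visit 1 section).** "A between groups statistical analysis of the pre- and postmenopausal cohorts will be conducted in a blind manner". The Abstract's methods paragraph says the same. The Visit 1 text then adds a linear mixed model with dose and/or group as fixed effects, described as exploratory. It also adds Bonferroni-adjusted post hoc comparisons across doses or between groups, and promises "Effect estimates with a 95% confidence interval for differences between groups". The levels of group and the pairs to be compared are not given.

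**Analysis of structure (end of the Visit 2 section).** "For between groups analyses (e.g., pre- vs. postmenopausal cohorts), data will be analysed using a one-way ANOVA".

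**The concern.** The contrast that justified recruiting 12 women per group appears nowhere in the analysis text as a comparison to be made. The contrast that is named, in three places, is a different one. As written, the hot-flush result would come either from a model labelled exploratory or from an adjusted post hoc pair.

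Three things are at stake:

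- **Standing of the result.** A reader of the final paper could not tell a planned hot-flush finding from a selected one.
- **Power.** A post hoc Bonferroni pair has less power than a single planned contrast on the same data.
- **Latitude.** The phrase about pre- and postmenopausal cohorts fits a two-group comparison (12 versus 24) and a three-group one. The two answer different questions, and nothing fixes the choice before the data are seen.

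**Working it through.** **Inputs.** Group sizes 12, 12 and 12, effect size 1 and power 0.9 come from the Sample size calculation section. Assumptions: effect size means a difference of 1 SD; SDs are equal; there are no dropouts; alpha is 0.05 two-sided. The sample size text states no alpha, but this value fits the 95% intervals promised for Visit 1.

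**1. The plan's own figure.** For two independent groups at d = 1 and 90% power, n per group ≈ 2(1.960 + 1.282)² / 1² = 21.0. The next whole number is 22, and the t-based calculation gives 22.02, so 23. One-sided at 0.05 it is 18. The stated 12 per group does not reproduce. That is a separate point, but it means the comparisons below start from well under 90%.

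**2. Hot-flush contrast as one planned comparison, 12 versus 12.** Noncentrality = d·√(n/2) = 1 × √6 = 2.449. With 22 degrees of freedom the critical t is 2.074 and power is 0.649. With the residual from all three groups (33 degrees of freedom) the critical t is 2.035 and power is 0.662. So about 65%.

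**3. The same contrast as one of three Bonferroni pairs.** Alpha per pair = 0.05/3 = 0.0167. Critical t is 2.591 (22 df) or 2.522 (33 df). Power is 0.459 or 0.480, so about 46–48%.

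**4. If the postmenopausal groups were pooled, 12 versus 24.** Suppose women with hot flushes differ by 1 SD and the other two groups are alike. The pooled difference is (0 + 1)/2 = 0.5 SD. Noncentrality with unit SD = 0.5 × √(12 × 24/36) = 0.5 × 2.828 = 1.414, which gives power 0.28. Simulation gives about 0.23, because mixing two different groups widens the spread in the pooled arm.

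**5. Dependence on the true pattern.** Simulated rejection rates; means are in SD units, in the order premenopausal, postmenopausal without, postmenopausal with hot flushes:

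| True means | Pooled pre v post | With v without hot flushes | Three-group ANOVA |
|---|---|---|---|
| 0, 0, 1 | 23% | 65% | 68% |
| 0, 1, 1 | 78% | 5% | 67% |
| 0, −0.5, 0.5 | 3% | 65% | 54% |

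In the second row the pooled test does well, but there is no hot-flush difference to find. In the third row the hot-flush difference is a full SD and the pooled test cannot see it. In the first row a three-level group factor avoids the loss from pooling.

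**The case against.** The best case for the plan is that this is an ambiguity and not a stated error, and much of that case stands.

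- **Pooling.** A reader might infer that the plan combines the two postmenopausal groups. No sentence says so. The objectives, the three columns of Table 1 and the 12 + 12 + 12 recruitment keep the groups apart, and Bonferroni adjustment between groups makes sense only with more than two. Equally, no sentence says they are analysed separately.
- **Only analysis.** A reader might say that pre- versus postmenopausal is the only between-group analysis. That is too strong: the Visit 1 text also has a group effect, post hoc comparisons and intervals. The Visit 2 text gives pre- versus postmenopausal as an example for a one-way ANOVA, which suits three groups. It is the only contrast *named*.
- **Halved effect.** The fall from 1.0 to 0.5 SD needs pooling and also asymptomatic postmenopausal women who match premenopausal women. It is not general, as the table shows.
- **Multiplicity.** A reader might count eight primary measures and infer a false-positive risk of 1 − 0.95⁸ = 34%. That requires independent tests. Conductance and sweat rate are recorded together at the same sites in the same women, so the documents do not support the figure. Nor is there a case here for demoting the sweat and structural outcomes: they come under "The primary outcomes relate to the assessment of skin function and structure", and structure is a full co-objective.
- **Level of detail.** Factor coding can be left to a full protocol or analysis plan that is not shown. But the article does name a contrast, and it is not the one that sized the study. That is a mismatch in what is stated, not an omission.

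**Conclusion.** The concern holds in a limited form. The contrast that sized the study is not named in the analysis text, the contrast that is named is a different one, and the status of the two postmenopausal groups is left open.

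In size: about 65% power if the hot-flush contrast is a single planned comparison, and about 46–48% if it is one of three Bonferroni pairs. If the groups were pooled and only women with hot flushes differed, power would be about 23%. If both postmenopausal groups shifted by 1 SD, the pooled test would have about 78% power but would say nothing about hot flushes. All of this rests on d = 1, equal SDs, no dropout and two-sided alpha 0.05.

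The documents do not support the claim that the plan pools the groups or that a hot-flush effect will be halved. Naming the contrast also does not restore the stated power of 0.9.

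**What to change.** In the Abstract's methods paragraph and the analysis text of Visits 1 and 2:

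1. Define group as three levels: premenopausal, postmenopausal without hot flushes, postmenopausal with hot flushes.
2. State that the two postmenopausal groups are not pooled.
3. Name with versus without hot flushes on the skin-blood-flow response as the planned primary contrast, outside the post hoc Bonferroni set and not labelled exploratory.
4. Report premenopausal versus postmenopausal without hot flushes as a further planned contrast.

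This is a change of wording, with no added participants, visits or measurements, and it should be settled before the groups are unblinded for analysis. The small downside is that the overall pre- versus postmenopausal comparison is no longer the headline result. The sweat and structural outcomes keep their present status.

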### Study aims

The overall aim of the study is to assess both function and structure of skin blood vessels and sweat glands in premenopausal and postmenopausal women. The specific objectives are:
1.To assess the responsiveness of skin blood vessels and sweat glands in premenopausal women and postmenopausal women with and without hot flushes.2.To examine the structure of skin blood vessels and sweat glands in premenopausal women and postmenopausal women with and without hot flushes.

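### Bonferroni on the three group comparisons is valid but inefficient; an overall test followed by unadjusted pairwise tests would hold the same 5% error per outcome and site with 5 to 18 points more power for the hot-flush contrast

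*Protocol article*

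**What the plan says.** The sample size section takes its basis from "previously reported differences in post-ganglionic skin blood flow responses between postmenopausal women with and without hot flushes". It then specifies "a power (1-β) of 0.9 and an effect size of 1" and concludes that "24 postmenopausal women (12 who experience hot flushes and 12 who do not) and 12 premenopausal women will be recruited". It gives no alpha, no sidedness and no allowance for multiple comparisons.

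The first objective covers all three groups: "To assess the responsiveness of skin blood vessels and sweat glands in premenopausal women and postmenopausal women with and without hot flushes".

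The statistical paragraph of Visit 1 (Cutaneous microdialysis, after Figure 1) describes the model: "Exploratory analyses using a linear mixed model with fixed effects of drug dose (cutaneous microdialysis) and/or group will be conducted". It then gives the multiplicity rule: "Post hoc* comparisons across drug doses or between groups will be completed using Bonferroni adjusted LSD". It does not say how many comparisons form the Bonferroni family. It does not make the pairwise tests conditional on a significant overall group test, and it does not exempt the contrast used for sizing. It promises 95% confidence intervals for group differences, which is the only hint that the overall level is 5%.

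**The concern.** Three groups give three pairwise comparisons. Read plainly, the rule puts the contrast that justified the sample size into a Bonferroni family with the two comparisons against premenopausal women, so it has to reach about one third of the usual alpha. In groups of 12 that costs a good deal of power.

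The cost is avoidable because three groups are a special case. Pairwise tests at full alpha after a significant overall test form a closed testing procedure:

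- If all three means are equal, any false positive must first pass the overall test, which limits the error to 5%.
- If exactly one pair is equal, there is only one true null among the pairs, and it is tested at 5%.
- If no pair is equal, no pairwise false positive is possible.

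Bonferroni is therefore not needed to hold 5% for the group effect, provided the overall test comes first. At stake is the chance of detecting the contrast on which the study was sized.

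**Working it through.** **Inputs from the protocol article.** Three groups of 12; effect size 1, read as a standardised mean difference d; stated power 0.9; 8 doses per drug site.

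**Assumptions.** Overall level two-sided 5%; Bonferroni family equal to the three group pairs; normal data with common variance; pooled error on 36 − 3 = 33 df.

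**Step 1. The stated power.** For two independent groups at two-sided 5%, d = 1 with 90% power needs 23 per group by the noncentral t distribution (22 by normal approximation); one-sided it needs 18. With 12 per group the power is 0.65 on 22 df and 0.66 on 33 df. The stated 0.9 is not reproduced even without any adjustment.

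**Step 2. Level under Bonferroni.** 0.05 / 3 = 0.0167.

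**Step 3. Power for the hot-flush contrast.** The noncentrality is d / √(1/12 + 1/12) = 1 / √(1/6) = 2.449. Power is the probability that |t| on 33 df exceeds the critical value.

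| Two-sided level | Critical t (33 df) | Power at d = 1 |
|---|---|---|
| 0.05 | 2.035 | 0.662 |
| 0.0167 | 2.522 | 0.480 |

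**Step 4. Gated procedure.** The overall F test on 2 and 33 df is done at 5% and, if significant, the pair is tested at 5%. Power depends on the premenopausal mean, so it was simulated (400,000 trials per setting; no-flush mean 0, hot-flush mean 1).

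| Premenopausal mean | Bonferroni | Gated, 5% | Gain (points) |
|---|---|---|---|
| 0.5 (midway) | 0.482 | 0.529 | 4.7 |
| 0 (equal to no-flush) | 0.480 | 0.589 | 10.9 |
| 1 (equal to hot-flush) | 0.481 | 0.591 | 11.0 |
| −0.5 (outside the range) | 0.479 | 0.653 | 17.4 |
| −1 (further outside) | 0.481 | 0.662 | 18.1 |

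**Step 5. A larger effect.** At d = 1.4, where unadjusted power is about 0.91, Bonferroni gives 0.81. The gated procedure gives 0.84 (premenopausal mean midway), 0.89 (equal to the no-flush group) and 0.91 (0.7 SD below it), a gain of about 3 to 10 points.

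**Step 6. Family-wise error.**

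| Configuration | Ungated, 5% | Gated, 5% | Bonferroni |
|---|---|---|---|
| All three means equal | 11.9% | 5.0% | 4.3% |
| Two equal, third 1 SD away | 5.0% | 4.8% | 1.7% |
| Two equal, third 2 SD away | 5.0% | 5.0% | 1.7% |

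One setting at d = 1.4 printed 5.06% for the gated procedure. The simulation standard error is √(0.05 × 0.95 / 400,000) = 0.03 points, so this is compatible with 5%.

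**Step 7. If the family also counts doses.** Three pairs at 8 doses give 24 comparisons and a level of 0.05 / 24 = 0.0021. Power at d = 1 is then about 0.21. The three-group argument does not cover comparisons at individual doses.

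**The case against.** **Bonferroni is a valid, standard and conservative choice.** This stands. The protocol says nothing false by using it, and a reader should not infer that it is an error.

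**The correction might be called unnecessary, with nothing gained in error control.** That stronger reading is tempting but the document does not support it. It is true only behind an overall test, and the protocol does not state one; the term post hoc suggests a gate but does not fix it. Without the gate, dropping Bonferroni gives a family-wise error of about 12% when all means are equal, against 4.3% with it. Even with the gate, Bonferroni pushes the error below 5%. What it does not do is supply protection that is needed to reach 5%.

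**The 0.0167 level and the family of three are inferred.** This stands. Three is the smallest family that covers all group pairs; a larger one would raise the cost. The article also does not say outright that the sized contrast is decided at the post hoc step, although it exempts nothing from the rule.

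**The protection is narrow.** This stands. It covers one group effect on one outcome at one drug site. It does not extend over the several primary outcomes, the three sites or the individual doses.

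**Bonferroni permits simultaneous intervals; gated testing does not.** True, though the article promises 95% intervals without calling them simultaneous.

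**The main shortfall is the sample size.** This stands. It would be wrong to infer that removing Bonferroni repairs the power.

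**One could test the hot-flush contrast alone at 5%, without a gate, and adjust the other two pairs between themselves.** This does not meet the same standard: when all means are equal, 5% plus two tests at 2.5% gives a family-wise error of about 8.3%.

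**The one-way ANOVA for the biopsy data (Visit 2) might seem to need the same correction.** It does not. No Bonferroni rule is written there.

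**Conclusion.** The point holds as a cheap gain in efficiency. If the level is two-sided 5% and the family is the three group pairs, the written rule gives the hot-flush contrast a power of about 0.48 at d = 1 with 12 per group. An overall test followed by unadjusted pairwise tests gives 0.53 to 0.66 and still holds the family-wise error at 5% for that outcome and site. The upper end of the gain requires a premenopausal mean outside the range of the two postmenopausal groups, and the article gives no figure for that mean; the lower end applies if it lies midway. The calculation treats the group effect as one summary value per woman with normal errors. The conclusion does not extend to dose-by-dose comparisons.

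**What to change.** In the statistical paragraph of Visit 1, limit the Bonferroni rule to comparisons across doses and to group comparisons at individual doses. For the overall group effect on each outcome and drug site (for example EC50 or the mixed-model group effect), use wording such as: *The three-group effect will be tested at two-sided 5%. Only if it is significant will the three pairwise group differences be tested, each at 5% without further adjustment.*

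In the sample size section, state the alpha, the sidedness and the test to which the power figure refers.

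The change is a few sentences, to be made before any unblinded analysis, with no further participants or measurements. Three costs should be acknowledged:

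- The pairwise 95% intervals will not be simultaneous.
- Error control applies per outcome and site only.
- If the premenopausal group differs but the two postmenopausal groups do not, the error rate for the hot-flush contrast rises from about 1.7% to the nominal 5%.
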